##### Phase angle difference (PAD)

PAD will be calculated by determining the number of hours between DLMO and average sleep mid-point (clock time of sleep onset–final morning awakening/2) over actigraphy.

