#### Light therapy effectively treats acute sad and correction of circadian phase is mechanistic of its antidepressant effects

Light therapy (LT) is the established, most researched, acute SAD treatment. Meta-analyses show that 53% of SAD patients fully remit (and 47% do not) over an LT trial [15]. Clinical practice guidelines recommend solo LT as a first-line acute SAD treatment and reinitiating daily LT each fall from first symptom until spontaneous springtime remission [16, 17]. However, only 41% of those treated acutely with LT continue using it over subsequent winters [18]. Several studies support circadian rhythm disturbances in SAD patients, with their circadian phase occurring either later (phase delayed) or, less commonly, earlier (phase advanced) compared to their euthymic circadian phase position following remission with LT [19–22] or to healthy individuals in winter [19, 22]. As restoring the correct phase of circadian rhythms is supported as LT’s mechanism of action [15, 23–25], circadian phase measures are established biomarkers of LT’s target and effect. We will use the best established method, dim light melatonin onset (DLMO), along with wrist actigraphy, an objective measure of sleep/wake patterns, to calculate Phase Angle Difference (PAD) = DLMO–mid-sleep [21].

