### Outcomes {12} (Table 1)

#### Primary outcome: structured interview guide for the Hamilton Rating Scale for Depression—Seasonal Affective Disorder Version (SIGH-SAD

The SIGH-SAD (42) includes the 21-item Structured Interview Guide for the Hamilton Rating Scale for Depression (HAM-D) and a supplementary 8-item subscale to assess atypical depressive symptoms associated with SAD. A trained rater, blind to treatment condition, will administer the SIGH-SAD at pre-treatment, treatment weeks 1–5, post-treatment, and winter follow-ups. The rater will always begin by asking if any new treatment other than the study treatment has been initiated and if any medications have changed. This will be coded in the database and considered as a possible covariate. A second blinded rater will rate audio-recordings of the SIGH-SADs to assess inter-rater reliability. The depression recurrence (primary outcome) criteria define SAD episode onset or recurrence [62] and were used in our prior trials: total SIGH-SAD score ≥ 20 + HAM-D score ≥ 10 + atypical score ≥ 5. Remission at treatment endpoint is classified by satisfying one or both of the following criteria [62]: (1) pre- to post-treatment reduction in total SIGH-SAD score ≥ 50% + HAM-D score ≤ 7 + atypical score ≤ 7, OR (2) HAM-D score ≤ 2 + atypical score ≤ 10. The same criteria will be applied to winter follow-up remission status by comparing follow-up to pre-treatment scores. We will follow our published SIGH-SAD protocol for item scoring rules, rater training procedures, and resolving rater discrepancies [63]. SIGH-SADs were administered live until March 2020 when we shifted to HIPPA-compliant videoconference due to the COVID-19 pandemic.

**Table 1 Tab1:** Measures and assessment schedule

Measure	Construct assessed	Metric	Pre-TX	Weekly during TX	Mid-TX*	Post-TX*	Winter 2	Winter 3
SIGH-SAD [42] (see description)	SAD recurrence (primary outcome) and remission status, symptom severity	Categorical recurrence status, categorical remission status, score	X	X	X	X	X	X
Beck Depression Inventory-II (BDI-II) [52]	Depression symptom severity, remission status (BDI-II ≤ 8)	Score, categorical remission status	X	X	X	X	X	X
Beck Anxiety Inventory [53]	Anxiety symptom severity	Score	X		X	X	X	X
Dim light melatonin onset (DLMO)	Circadian timing	Clock time (military)	X			X	X	X
Wrist actigraphy and Pittsburgh Sleep Diary [54]	Sleep & circadian timing; daytime activity	Mean mid-point of sleep; mean daily activity count	X			X	X	X

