^†^Phase angle difference (PAD)	Circadian timing	DLMO–mid-sleep (from actigraphy)	X			X	X	X
^†^PIPR	Post-illumination pupil response	Net PIPR (red–blue light response)	X		X	X	X	X
^‖^Pupil dilation and sustained frontal gamma-band EEG responses to negative and winter words	Prefrontal engagement as it relates to emotion elaboration and regulation	Mean pupillary and sustained frontal gamma responses 2–10 s following emotional word onset	X		X	X	X	X
^‖^Seasonal Beliefs Questionnaire (SBQ) [32]	Maladaptive thoughts about the seasons and light availability	Score	X		X	X	X	X
^‖^Dysfunctional Attitudes Scale-Form A (DAS) [55]	Depressive schemas	Score	X		X	X	X	X
^‖^Behavioral Activation for Depression Scale (BADS) [56]	Self-reported behavioral activation	Score	X		X	X	X	X
^†^Composite Scale of Morningness (CSM) [57]	Chronotype	Score	X		X	X	X	X
Treatment Credibility Scale [58]	Credibility for the CBT-SAD and LT treatment conditions	Score	X		X	X		
Millon Clinical Multiaxial Inventory—Fourth Edition (MCMI-IV) [59]	DSM-5 personality disorders	Scale scores, possible DSM-5 personality disorders	X					
Quality of Life Enjoyment and Satisfaction Questionnaire (Q-LES-Q) [60]	Quality of life related to: physical health, mood, leisure time activities, social relationships, general activities, work (if applicable), household duties (if applicable), and school/coursework	Score	X			X	X	X
Sheehan Disability Scale (SDS) [61]	Mental-health related impairment in work, social life/ leisure activities, and home life/family responsibilities	Score	X			X	X	X
MOS SF-20 (62)	Health-related quality of life	Score	X			X	X	X
SCID-5-RV major depressive episode criteria	Recurrences between post-treatment and winter 2 and between winters 2 and 3	Categorical recurrence status					X	X

*Repeated in winter 2 if switched to the alternate treatment

^†^Candidate mediator of LT’s effects

^‖^Candidate mediator of CBT-SAD’s effects. TX-treatment

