##### PIPR

The PIPR will be assessed using previously validated methods in SAD [26, 31]. The PIPR metric is calculated as the difference between pupil responses to red and blue light, as only responses to blue light reflect the circadian system. Due to daily variation in retinal responsivity, participants will undergo PIPR testing only during the daily plateau in responsivity. Stimuli are electronically controlled via light emitting diodes within the DP2000 Neuroptics (Irvine, CA) pupilometer goggles. Stimuli are 22.68 nm full width half-maximum (FWHM; 467.7 nm blue light) and 15.78 nm FWHM (632.9 nm red light) and both are calculated to yield a retinal irradiance of 13.5 log photons/cm^2^/s as measured radiometrically (USB4000 Spectrometer, OceanOptics, Dunedin, FL). Calculated retinal irradiance accounts for age-related lens density and the difference in transmission of red and blue wavelengths through the lens [65]. We will use lights of equal retinal irradiance (13.5 log photons/cm^2^/s) stimuli of 200 ms based on Park et al. [66]. The red and blue exposures will be alternated four times each. Our irradiance is comparable to Gamlin et al. [30] (13.5–14.1 log photons/cm^2^/s) and Zele et al. [67] (14.2 log photons/cm^2^/s). Pre-processing via MATLAB (Natick, MA) for the PIPR includes [1] blink removal, [2] averaging the pupil area, and [3] calculating Net PIPR. Linear interpolation is used to define and replace blink data points using co-investigator’s (K.A.R.) laboratory’s standard methodology [31]. The PIPR will be analyzed for 30 seconds, beginning 10s after light OFF, and both blue and red PIPR will be calculated as a percentage of baseline constriction 7 s prior to stimulus onset. We use an 11 min dark adaptation period just prior to testing, and 45 min in dim light prior to that (< 50 lux). We are using 2 min intervals between stimuli to reduce potential cumulative effect of repeated stimuli. We average all four trials for red and blue, regressed on calculated retinal irradiance for each trial, and then calculate a Net PIPR (blue–red). One of the benefits of the Net PIPR is that drug effects are expected to affect the PIPR response to both blue and red light similarly. The main difference between the red and blue PIPRs is that the blue PIPR includes responses due to intrinsically photosensitive retinal ganglion cells (ipRGCs), while the red does not. Subtracting the red response from the blue leads to a Net PIPR value excluding all influences on pupil dilation except the ipRGC effect. Therefore, effects on pupil dilation of caffeine, nicotine, antidepressant medications, alcohol, exercise, diet, or even autonomic regulation, as examples, in SAD will be controlled mathematically with Net PIPR.

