To examine mechanistic differences between CBT-SAD and LT, mixed effects linear regression with subject as a random effect will be used to model biomarker changes during treatment as a function of time, treatment, and their interaction. We will also model the relationship between biomarker change and change depressive symptoms as a function of treatment by letting the regression coefficient differ between CBT-SAD and LT. This will provide a test of whether potential mediators of effect are treatment-specific. The predictive value of biomarkers at baseline, their pre-post treatment change, and the persistence of the change at follow-up will be examined using logistic regression (for post-treatment remission and winter 2 recurrence) and linear regression (for SIGH-SAD and BDI-II scores) with post-treatment and winter 2 outcomes as dependent variables. Interactions between the biomarkers and treatment will be used to test if the associations with outcomes differ in the CBT-SAD and LT groups. Adherence will be included in ancillary analyses to test its effect on the relationships of treatment with biomarkers and LT or CBT-SAD outcomes. The relationships between biomarkers and outcomes will be validated by examining how well they predict post-treatment and winter 3 outcomes for subjects who experience a recurrence at winter 2 and are switched to the alternative treatment. Data from the cross-over subjects will also be analyzed using mixed linear regression to compare within-person differences in pre-treatment biomarkers and their changes during their initial and subsequent treatments. Treatment, time point (winter 1 or 2), and their interaction will be included to test the effect of treatment sequence on within-person differences in biomarker responses to CBT-SAD and LT.

##### Aim 3

Logistic and linear regressions similar to those for Aim 1 will be used to compare the effect of switching from CBT-SAD➔LT versus LT➔CBT-SAD on winter 3 recurrence and depression scores. Post hoc adjustment for any differences between switch groups in baseline characteristics, treatment response, and biomarker profiles will be done by including them as covariates. Mixed linear regression will be used to longitudinally model depression scores over the three winters, with treatment as a time-varying covariate.

##### Aim 4

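### Two light-therapy biomarker definitions need correcting: the printed sleep mid-point formula does not give a mid-point, and Net PIPR is subtracted in opposite directions in Table 1 and in the methods

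*Protocol article*

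**What the plan says.** **PAD.** The Introduction defines "Phase Angle Difference (PAD) = DLMO–mid-sleep", and the PAD row of Table 1 uses the same signed difference. The sleep metric in Table 1 is "Mean mid-point of sleep". The section headed Phase angle difference (PAD) gives the only operational rule. It obtains PAD by "determining the number of hours between DLMO and average sleep mid-point (clock time of sleep onset–final morning awakening/2) over actigraphy", and does not say which is subtracted from which.

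**Net PIPR.** Table 1 gives the metric as "Net PIPR (red–blue light response". The PIPR section says the four red and four blue trials are averaged and that the team will "then calculate a Net PIPR (blue–red". It then confirms in words that the red response is taken away from the blue one.

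**Use.** The Objectives call PAD the established biomarker of the target of light therapy (LT) and list the PIPR as exploratory. Both enter the Aim 2 models and, as candidate mediators, the Aim 4 growth-curve models. The Sample size section expresses biomarker-outcome associations as odds ratios per 1 SD increase in the biomarker or its change.

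**The concern.** A derived variable is only as good as its written rule. Biomarker data are processed at one university and sent as a finished database to the biostatistician at another (Data management). The written definition is therefore what lets the analyst know what a value and its sign mean.

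For PAD, a mid-point computed as printed would be wrong for every participant, by an amount that depends on the person's own sleep times. For Net PIPR, the Introduction's hypothesis is directional: people with SAD have a reduced response in winter. If the file follows one convention and the analyst reads it under the other, a normalising response is reported as a worsening one. No test statistic would reveal the mistake.

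**Working it through.** **The plan's own figure first.** The Sample size section claims 80% power for a 0.45 SD biomarker difference with 80 per arm. Two-sided alpha of 0.05 is assumed, as none is stated. Power = Φ(0.45 × √(80/2) − 1.96) = Φ(2.846 − 1.960) = 0.81; a two-sample t-test also gives 0.81. The figure reproduces. It is in SD units, so neither definition below alters it.

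**Mid-sleep.** The clock times here are illustrative: onset 23:00, final awakening 07:00, DLMO 21:00.

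| Reading | Arithmetic | Result |
|---|---|---|
| True mid-point, continuous clock | 23 + (31 − 23)/2 = 27 | 03:00 |
| Onset − (awakening/2) | 23 − 7/2 = 19.5 | 19:30 |
| (Onset − awakening)/2, raw clock | (23 − 7)/2 = 8 | 08:00 |
| (Onset − awakening)/2, continuous clock | (23 − 31)/2 = −4 | −4 h: minus half the sleep duration, not a time of day |

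The correct PAD is 21 − 27 = −6.0 h. With 19:30 it becomes 21 − 19.5 = +1.5 h, which has the wrong sign. With 08:00 taken as the next morning it is 21 − 32 = −11 h.

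The error is not constant. Move the sleep period one hour earlier, to 22:00–06:00. The true mid-point moves by one hour, to 02:00. The first literal reading gives 22 − 6/2 = 19.0, a move of half an hour. The second gives (22 − 6)/2 = 8, no move at all. Pre-post changes in PAD would be distorted as well as levels.

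Midnight also matters. For onset 00:30 and awakening 08:00 the true mid-point is 0.5 + 7.5/2 = 4.25, or 04:15. The literal readings give 0.5 − 8/2 = −3.5 and (0.5 − 8)/2 = −3.75. Even the probable intent, half the sum of the two times, gives (23 + 7)/2 = 15:00 on raw clock times in the first example, which is 12 h out. The unwrapping rule therefore belongs in the definition.

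**Hours between.** DLMO precedes mid-sleep in these examples, so this wording gives +6.0 h where DLMO minus mid-sleep gives −6.0 h. It is the same score with the sign reversed, and it differs from the Introduction and Table 1.

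**Net PIPR.** Red − blue = −(blue − red). A linear coefficient b becomes −b with the same standard error and two-sided p-value. An odds ratio becomes its reciprocal. For example, the 2.2 per SD that the Sample size section uses for the LT group becomes 1/2.2 = 0.45, the same distance from 1 on the log scale. The dash in Table 1 is a subtraction, because the PAD row uses it that way.

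The direction of subtraction does not by itself fix the meaning. The PIPR section averages pupil area and then expresses responses as a percentage relative to baseline. If the value is remaining pupil size, sustained constriction to blue makes blue − red negative, and a stronger response is a lower number. If the value is amount of constriction, a stronger response is a higher number. The text does not settle which applies.

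**The case against.** The best defence is that both items are editorial. Mid-point is named correctly in several places, the dash in the formula may have been meant as a range from onset to awakening, and experienced collaborators process the actigraphy. Nobody would accept 19:30 as the middle of a night slept from 23:00 to 07:00. For Net PIPR, the methods text is the operative one and spells out the subtraction. The PIPR is exploratory, and the Introduction describes the deficit by size. Most of this stands: the intent on mid-sleep is clear, and nothing shows that data were computed wrongly. It does not make the printed rule correct, since half of an onset-to-awakening interval is a duration, not a time. Nor does it reconcile Table 1 with the methods.

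A reader might go further and infer that PAD is mis-modelled. The Introduction describes patients "with their circadian phase occurring either later (phase delayed) or, less commonly, earlier (phase advanced) compared to their euthymic circadian phase position", so a signed linear score could treat the same shift as correction in one person and worsening in another. The document does not establish that as an error:

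- The Aim 2 and Aim 4 models are described for all biomarkers together, and a PAD-specific term is a matter for an analysis plan that is not shown.
- The Aim 2 sentence stating that mixed regression "will be used to model biomarker changes during treatment as a function of time, treatment, and their interaction" is the phase-shift model, for which signed PAD is the natural scale.
- The Light therapy section states a delay-correction hypothesis, which suits a one-directional score.
- The share of phase-advanced participants, the relative slopes in the two groups and a single reference PAD are all absent, so any loss from a signed linear PAD cannot be quantified.

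**Conclusion.** The point holds for two definitions. The sleep mid-point formula is wrong as printed and conflicts with Table 1. Taken literally, it turns a PAD of −6 h into +1.5 h or −11 h in the worked example and distorts change scores too. It is most likely a notation error, and the size of any effect depends on whether anyone applied it literally, which the document cannot show. The Net PIPR conflict is a direct contradiction. It reverses the sign and reading of coefficients and odds ratios but not their magnitude, p-values or power.

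Both concern the mechanism aims only. The primary comparison of winter 2 recurrence and the stated sample size and power are unaffected. The choice of a signed linear PAD is not shown to be a fault.

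**What to change.** 1. In the PAD section, replace the parenthesis with: mid-sleep = onset + (final awakening − onset)/2, computed per night on a clock unwrapped across midnight, then averaged over the actigraphy week.
2. Replace the hours-between wording with the signed PAD = DLMO − mid-sleep of the Introduction and Table 1, on the same continuous clock.
3. Give Net PIPR one direction in Table 1 and in the PIPR section. State whether the underlying percentage is pupil size or amount of constriction, and whether a larger Net PIPR means a stronger or weaker melanopsin response.
4. Check the existing processing code at both sites against these definitions before the biomarker file is merged with outcomes.

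Optional, as a sensitivity analysis only: since the Introduction allows delay or advance while the Light therapy section assumes delay, the PAD-outcome models could add a PAD-change by baseline-phase interaction. This would require baseline phase to be defined in advance.

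Items 1 to 3 are a few lines of text and item 4 is a short code check. No new data, sample size change or change to the primary analysis is needed.

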##### EEG/pupillometry

Responses to emotional and seasonal words using a word-valence identification task [38] will be measured using pupil dilation (via infrared pupillometry as described for the PIPR) and frontal gamma-band EEG responses. Stimuli will include emotionally salient words (positive, negative, and neutrally valenced words; 20 each) and seasonal words (winter and summer words; 20 each) presented using E-prime (Psychology Software Tools, Pittsburgh, PA). Word corpi were generated by selecting words with minimal semantic distance from seed words in the GoogleNews corpus (described at https://code.google.com/archive/p/word2vec/#Pre-trained_word_and_phrase_vectors) balanced for word length, frequency, and predicted valence and arousal. The corpus contains approximately 1 billion words, from which 3 million words and phrases have been subjected to machine learning to derive 300 features which, together, predict the probability that any term will occur within a small proximity of another term in the corpus. This technique has been shown to effectively code the words for content [68] using the cosine between the feature vectors as a contextual similarity metric. Valence and arousal predictions were generated based on training a feature classier on normative word ratings from the affective norms for English words (ANEW) [69] word set using seed words for negative (“negative” and “sad”), neutral (“neutral,” “calm,” “unemotional”), positive (“positive,” “happy”), summer (“summer,” “summertime,” “light”), and winter (“winter,” “wintertime,” “dark”). The task design will be largely as we have used in the past [38], though with words presented out loud using text-to-speech recordings to avoid light-reflex responses, following a fixation cross, using an inter-stimulus interval of 8 seconds. The stimulus word lists are displayed in Table 2.

**Table 2 Tab2:** Stimulus words in the word-valence identification task

Stimulus category				
Seasonal words		Emotionally salient words		
Winter	Summer	Negative	Positive	Neutral
Blizzard Chill Cloudy Cold Damp Darkness December Dreary February Frost Gray Hibernate Icy Indoors Sledding Snow Snowshoeing Snowy Windy Winter	August Autumn Boating Brightest Camp Getaways Heat Hot July June May Midsummer Outdoors Picnics Spring Summer Sunny Sunshine Vacation Warm	Awful Bad Biased Bothers Disgusting Frustrating Hateful Horrendous Horrible Horrid Hostile Negative Shameful Sorry Terrible Ugly Unhelpful Unpleasant Weird Worrying	Cheerful Confident Constructive Delighted Exciting Fantastic Fortunate Grateful Happy Healthy Pleased Satisfied Successful Supportive Terrific Thankful Thrilled Upbeat Uplifting Welcoming	Agnostic Analyst Cautious Dull Flat Hold Impartial Intact Lowered Mediate Preferred Purely Rating Sell Sided Subjective Tact Tense Unbiased Upgraded

Task data will be conducted during a restricted daytime window of assessment, and time of testing as well as individual chronotype or DLMO values will be explored as covariates in analyses to compensate for daily variations in positive affect as well as cognitive influences such as reaction time.

Pupillary reactivity will be collected using the same hardware described for the PIPR, with preprocessing (linear interpolation through artifacts and blinks, averaging of pupillary waveforms across trials within conditions) as in Siegle et al. [70] with mean pupillary reactivity during trials minus a pre-stimulus baseline being evaluated per participant as a dependent measure.

EEG will be measured with BioSemi (Cortech Solutions, Wilmington, NC) ActiveTwo amplifiers at 32 sites using a sampling rate of 250 Hz (1 samp/4 ms) and a .02–100 Hz band-pass filter, subjected to average referencing, artifactual channel interpolation and continuous Morlet wavelet transformation with mean signal, per electrode, in the gamma band region (30–45 hz) extracted as in Kerr et al. [71]. Frontal gamma will be defined as the mean signal across all collected frontal electrodes (Fp1, AF3, F7, F3, FC1, FC5, FC6, FC2, F4, F8, AF4, Fp2, Fz) minus a pre-stimulus (fixation) baseline of 100 ms with secondary analyses [1] separating left and right frontal gamma measures and [2] examining sample-wise tests along extracted pupillary and EEG frontal gamma waveforms to identify temporal intervals of group and condition-related variation, controlling type I error using temporal contiguity thresholding, as in Siegle et al. [70].

